## Abstract

**Background:**

The prevalence of central obesity is constantly increasing, and visceral fat is associated with increased production of inflammatory factors and metabolic risk factors. Lutein might retard the development of metabolic disease through its antioxidant and anti-inflammatory properties. Furthermore, epidemiological studies have associated higher dietary intake and serum levels of lutein with decreased adiposity. However, few randomised controlled trials have shown the effects of lutein supplementation on inflammatory biomarkers and metabolic risk factors, especially in adults with central obesity.

**Methods:**

This study will be conducted as a double-blind, parallel placebo-controlled clinical trial in which 120 people who have central obesity, are 18 to 60 years old and are willing to provide informed consent will be randomly assigned to the intervention or placebo group in a 1:1 ratio according to sex, age and waist circumference. The intervention group will receive 10 mg daily lutein supplementation for 12 weeks to explore the effect of lutein supplementation on serum lutein, glycaemic and lipid profiles, inflammatory factors and body composition. Two populations (intention-to-treat population and per-protocol population) will be used in the data analyses.

**Discussion:**

Our findings from this trial will contribute to the knowledge of the association between lutein supplementation and inflammatory biomarkers and metabolic risk factors in people with central obesity and will offer a possibility for the prevention of inflammatory diseases.

**Trial registration:**

Chinese Clinical Trial Registry: ChiCTR1800018098. Registered on 30 August 2018.

## Introduction

The prevalence of obesity has constantly increased and has reached epidemic proportions. The World Health Organization estimated that, by 2016, 39% of adults 18 years or over were overweight and 13% were obese worldwide [1]. Obesity represents a major risk factor for an expanding set of chronic diseases, such as type 2 diabetes mellitus, hypertension, cardiovascular diseases and cancer [2–4]. Specifically, central obesity, which occurs when excessive abdominal fat is deposited around the stomach and abdomen, is considered to be the most detrimental type of obesity and is accompanied by an increased risk of mortality [5, 6]. Substantial studies have suggested that oxidative stress and inflammation may be mechanistic links between obesity and metabolic diseases [7].

It is clear that the levels of oxidative stress and inflammatory factors increase as the amount of adipose tissue increases. The adipokines—interleukin-6 (IL-6), tumour necrosis factor-alpha (TNF-α), adiponectin, leptin and resistin—secreted by adipose tissue play a role in the homeostasis of various physiological processes, such as insulin sensitivity, energy expenditure and fatty acid oxidation [8, 9]. However, compared with other fat deposits, visceral fat has more adverse effects, including higher levels of free fatty acids, inflammatory molecules, and adipocytokines [10–13]. Epidemiological studies have indicated that visceral fat is correlated with insulin resistance (IR) and glucose intolerance and increasing levels of C-reactive protein (CRP), TNF-α, IL-6, isoprostanes and monocyte chemoattractant protein-1 (MCP-1) [13, 14].

Lutein is an oxygenated carotenoid that is found primarily in dark green leafy vegetables and egg yolks. Lutein is known mostly for its effects on visual function and its preventative effect against macular degeneration, potentially acting as an antioxidant that protects against light-induced oxidative damage in the retina by oxygen radicals [15, 16]. Given the beneficial antioxidant and anti-inflammatory properties [16], it is hypothesised that lutein may have beneficial effects on inflammatory biomarkers and metabolic risk factors. Xu et al. [17] provided lutein supplementation to patients with early atherosclerosis and found that the intervention group had significant decreases in serum IL-6 and MCP-1. An intervention study conducted in healthy non-smokers revealed that lutein supplementation increased total antioxidant capacity and reduced CRP [18]. Although accumulating epidemiological studies have shown an inverse relationship between serum carotenoid concentrations and circulating markers of inflammation, such as CRP and soluble intercellular cell adhesion molecule-1 (ICAM-1), intervention studies have focused mostly on other carotenoids, such as lycopene [19, 20], and less on lutein.

Another hypothesis is that lutein may have anti-adiposity effects. Our previous study found that lutein treatment significantly decreased body weight and abdominal and total adipose tissue, which were increased by high-fat-diet feeding in mice [21]. In addition, the concentrations of total cholesterol (TC) and triglycerides (TGs) in the serum and liver and the serum levels of low-density lipoprotein cholesterol (LDL-C) were significantly reduced [21]. Also, epidemiological studies have associated higher dietary intakes and serum levels of lutein with decreased adiposity [22–24]. However, despite animal studies and human epidemiological studies linking lutein to adiposity, there is a paucity of randomised controlled trials (RCTs) using lutein supplementation to assess changes in adiposity.

An important aspect to consider with lutein supplementation is that it cannot be synthesised by humans and can be obtained only through diet or supplements. However, our previous study revealed that the median intake of lutein (2.499 mg/d) is far below the special proposed level (10 mg/d) that is recommended in the 2013 Chinese Dietary Reference intakes [25]. In addition, although the antioxidant properties of lutein have been proven in different populations, reports dealing specifically with lutein in people with central obesity are scarce. In light of the information above, providing lutein supplementation to people with central obesity is worthy of exploration.

## Methods

### Study design and setting

This is a double-blind, parallel RCT enrolling participants with central obesity. The Standard Protocol Items: Recommendations for Interventional Trials (SPIRIT) 2013 statement will be followed in this trial (Additional file 1: SPIRIT checklist) [26]. The proposed clinical trial will be conducted at the Community Health Service Centre (CHSC) in Nanshan District, Shenzhen, Guangzhou Province, China, for 12 weeks to assess the effects of lutein supplementation (10 mg/d) on inflammatory biomarkers and metabolic risk factors in adults with central obesity. Figure 1 illustrates the overview of the study.

**Fig. 1 Fig1:**
[figure not shown]
Flowchart of the trial

### Study participants and eligibility criteria

It is estimated that 52 participants per treatment group would be required for 80% power and a 5% level of significance to detect the change in serum TGs over 12 weeks of supplementation [27]. Allowing for a dropout rate of about 15%, we aim to recruit 120 participants in total. Participants were eligible for this study if they fulfilled the following criteria: (1) age between 18 and 60 years, (2) waist circumference (WC) of at least 90 cm for males and at least 85 cm for females, (3) deficient lutein intake (dietary lutein intake of less than 10 mg/d), and (4) willingness to sign the informed consent form. People meeting any of the following criteria will be excluded from participation: (1) use of lutein supplementation or related health-care products within 1 month, (2) use of antibiotics within 1 month, (3) secondary obesity, (4) adoption of a special diet or meal replacement in the previous 2 weeks, (5) use of insulin or insulin sensitizers within 1 month, (6) chronic diseases (including type 2 diabetes, hypertension and dyslipidaemia) for over 10 years, (7) hepatorenal dysfunction (creatinine of more than 1.2 times the upper normal limit of creatinine, aspartate aminotransferase (AST) of more than 1 time the upper normal limit), (8) any active tumours/cancers, (9) regular use of drugs affecting blood lipid, (10) pregnancy or lactation or (11) history of gastrointestinal surgical operation.

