#### Study outcomes

The primary outcome consists of changes in the inflammatory biomarkers between the intervention and placebo group from baseline (test visit 1) to 12 weeks later (test visit 2). The secondary objectives are to assess changes in the anthropometric indexes, including weight, WC, HC and body composition.

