### Statistical analysis

Two populations will be used in the analyses. The intention-to-treat (ITT) population will include all participants who have been randomly assigned, whereas the per-protocol (PP) population will include all participants who accomplish the entire intervention. The baseline characteristics of the study will be summarised as the means ± standard deviations for parametrically distributed data, geometric mean values (and 95% confidence intervals) for non-parametrically distributed data, and numbers (percentages) for categorical data.

Differences between participants who complete and withdraw from the trial will be analysed by using an independent *t* test or the Mann–Whitney test for continuous variables (e.g., age) and the chi-squared test for categorical variables (e.g., sex). For primary and secondary outcomes, analysis of covariance will be used to examine differences between lutein supplement and placebo at 12 weeks, adjusting for potential confounding factors and effect modifiers (e.g., baseline age and sex). The present study has no plan for subgroup analysis. Our statistical analysis will be performed by using R software, and the results will be considered significant at a *P* value of less than 0.05.

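### The only power calculation is for serum triglycerides, which are not a listed outcome, so 80% power is not established for the inflammatory-biomarker primary outcome

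*Protocol article*

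**What the plan says.** In the protocol article, the sample size is given under Study participants and eligibility criteria: "52 participants per treatment group would be required for 80% power and a 5% level of significance to detect the change in serum TGs" over the 12 weeks of supplementation, with a literature reference. The text continues: "Allowing for a dropout rate of about 15%, we aim to recruit 120 participants in total". It states no TG difference, standard deviation or sidedness.

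Under Study outcomes, "The primary outcome consists of changes in the inflammatory biomarkers between the intervention and placebo group" from baseline to 12 weeks. No single marker is named there. The secondary objectives in that section are anthropometric: weight, waist and hip circumference, and body composition.

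TGs appear elsewhere as one of the blood measurements in Table 2 and under Biological sampling. The abstract includes lipid profiles among the effects to be explored. None of these places gives TGs primary or secondary status.

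The Statistical analysis section plans analysis of covariance for primary and secondary outcomes at 12 weeks, and "the results will be considered significant at a *P* value of less than 0.05".

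**The concern.** A power statement holds for one endpoint, with that endpoint's assumed difference and variability. Here it is attached to TGs, while the trial will be judged on inflammatory markers. The 80% would carry over only if a marker's standardised effect were at least as large as the one implied for TGs, and the article does not claim that.

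The stake is how a null result is read. If the biomarkers show no significant difference, readers will see 80% power in the methods and may take the result as evidence of no effect. That figure was not calculated for any of the markers, so readers cannot tell an absent effect from one too small for this trial to see.

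**Working it through.** **Inputs from the article.** 52 per group, 80% power, 5% significance (Study participants and eligibility criteria); 1:1 allocation (abstract, Methods); about 15% dropout and 120 in total (Study participants and eligibility criteria).

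**Assumptions.** Two-sided testing; a two-sample comparison of means; no gain in precision from covariates.

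**1. The stated 52.** It cannot be reproduced forwards, because the TG difference and standard deviation are not given. Solved backwards with the normal approximation:

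d = (z₀.₉₇₅ + z₀.₈₀) × √(2/n) = (1.960 + 0.842) × √(2/52) = 0.549.

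The noncentral t gives 0.555. If the test were one-sided, d = (1.645 + 0.842) × √(2/52) = 0.488. So 52 per group is consistent with a TG effect of roughly half a standard deviation, but the article neither states nor confirms that value.

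**2. Does the powered variable match an outcome?**

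| Variable | Powered | Primary | Secondary |
|---|---|---|---|
| Serum TGs | yes | no | no |
| Inflammatory biomarkers | no | yes | no |
| Anthropometric indexes | no | no | yes |

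No listed outcome has a power calculation.

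**3. What 52 per group would give for one biomarker.** The article supplies no biomarker effect size, so this is a range of assumed values (two-sided 5%; power by noncentral t, required n by normal approximation):

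| Assumed standardised difference | Power with 52 per group | n per group for 80% |
|---|---|---|
| 0.2 | 17% | 393 |
| 0.3 | 33% | 175 |
| 0.4 | 52% | 99 |
| 0.5 | 71% | 63 |
| 0.55 | 79% | 52 |
| 0.6 | 86% | 44 |

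Power for the primary outcome could lie anywhere in this range or outside it. The article does not say where.

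**4. The dropout step.** 120 × 0.85 = 102, or 51 per group. Dividing by the retained fraction, 104/0.85 = 122.4, so 123 in total; by group, 52/0.85 = 61.2, so 62 per group or 124. Multiplying instead, 104 × 1.15 = 119.6, which matches 120. With 120 randomised, 52 per group is kept up to a loss of 1 − 104/120 = 13.3%. At d = 0.555, 51 per group gives 79.2% power rather than 80%.

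**5. Detectable difference for the actual primary outcome, 51 per group, 80% power, noncentral t.**

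- One biomarker at two-sided 5%: d = 0.560.
- Five biomarkers, each at 0.05/5 = 1%: d = 0.688. Power at d = 0.555 is then 57%.

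The five are the inflammatory markers in Table 2 (CRP, IL-6, IL-1β, MCP-1, TNF-α). Both that list as the definition of the primary outcome and the equal split are assumptions.

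**The case against.** The strongest reply is that the article claims nothing false. It ties the 80% openly to TGs and never says that it applies to biomarkers. The abstract and Discussion also describe a joint aim covering inflammatory and metabolic risk factors, and lipid profiles are named in the abstract, so TGs lie within the trial's purpose. This stands as far as it goes: sizing a trial on a metabolic variable of interest is not absurd. It does not remove the mismatch, because the section that defines the outcomes omits TGs and the primary outcome there has no power statement. This is not detail that an article may leave to a fuller document. Two statements in the article itself do not fit together.

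A reader might go further and infer that the trial is underpowered. The documents do not support that. Without an effect size or standard deviation for any biomarker, power is unestablished, not shown to be low.

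A reader might also treat the 57% and 0.69 as the trial's true operating figures. They are not. The article names no marker in its primary outcome. Table 2 also lists adiponectin and RBP4 on the same week 0 and week 12 schedule. No division of the 5% is specified, and multiplicity handling may be set out in an analysis plan not shown here.

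Finally, 120 might be called an arithmetic error. Against 123 or 124 the gap is about 3%, which is within the wording of about 15% and costs 0.8 percentage points of power. It is a minor point.

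**Conclusion.** The point holds. The article's only power figure, 80% with 52 per group, concerns change in serum TGs, which is neither a primary nor a secondary outcome. It therefore gives no support to the inflammatory-biomarker primary outcome. This is an inconsistency between two sections, and it should be corrected because it affects how the primary result will be read.

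The size can be stated only as a detectable difference: about 0.56 standard deviations for one biomarker with 51 completers per group, and about 0.69 at 1% per marker. The first figure rests on two-sided testing, 15% loss and no covariate gain; the second also rests on the five-marker assumption.

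**What to change.** Keep the target of 120 and rewrite the sample-size paragraph so that it agrees with Study outcomes:

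1. Say that the calculation for TGs does not power the primary outcome. Describe TGs as an exploratory variable, or give them a defined status under Study outcomes. Calling them secondary in the sample-size paragraph alone would contradict the present outcome list.
2. Add the difference detectable for the primary outcome. Suggested wording: *With about 51 completers per group, the trial has 80% power at two-sided 5% to detect a standardised difference of about 0.56 in one inflammatory biomarker. If the five inflammatory markers in Table 2 are each tested at 1%, the detectable difference is about 0.69.* Keep the second sentence only if the sponsor adopts that marker list and that split.
3. As a minor edit, give the expected completers as 51 per group at 15% loss, or say that 52 per group holds up to about 13% loss.

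The cost is one paragraph and no extra participants. The price is a stated power less favourable than the present one.

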### Randomisation and blinding

After the inclusion and exclusion criteria are assessed and informed consent is obtained, participants will be allocated to the lutein group or the placebo group. Computer-generated random numbers will be used for allocation sequence generation and stratification will be completed according to sex, age and WC. This part of the study will be performed by a person who is operationally independent from the study team. Allocation concealment will be implemented by using a random number card in a black envelope. The details of the allocation will be concealed from the investigators, outcome assessors and the patients until all data collection is complete. The collected data of the patients will be kept confidential during this trial.

### Supplements

The participants will receive either 10 mg of lutein or placebo capsules per day for 12 weeks. Lutein (10 mg) will be mixed with pregelatinous starch (240 mg) and provided in acid-soluble gelatine capsules, and the placebo will contain pregelatinous starch (250 mg). To maintain and guarantee blinding, the capsules will be identical in appearance, shape, smell and weight. All capsules will be provided by the Angel Nutrition Co., Ltd. (Yichang, China). Face-to-face instruction on how to take the capsules will be provided at baseline. The enrolled participants will be required to (1) take one capsule along with meals daily; (2) avoid making any changes to dietary habits, physical activity level (PAL) or medicine use; and (3) record changes in dietary habits, PAL and medicine use in a timely manner.

### Study procedures

#### Recruitment and screening

Table 1 provides the schedule for enrolment, intervention and follow-up. Participants will be recruited by placing advertisements on social media sites and community bulletin boards. Once a volunteer expresses initial interest in participating in the study, he or she will have face-to-face or telephone communication with the research assistant. Detailed information on the study trial, including the purpose, the methods of the intervention and duration, will be provided to the volunteers. If they are still interested in this project after careful consideration, the structured standardised screening questionnaire, which is based mainly on the inclusion and exclusion criteria for the study, will be used to assess the potential eligibility of the participants for the study. Potential participants who are found not to be eligible will be excluded at this stage. Eligible participants will be invited to attend a further screening visit, which will take place at the CHSC. First, informed consent will be obtained from all participants. Second, for safety assessments, liver and renal function will be evaluated by collecting fasting blood samples and spot urine samples. Third, the anthropometric index will be measured by the trained investigators.

**Table 1 Tab1:** Schedule for screening, intervention and follow-up (test visit)

	Screening (−4 week)	Test visit 1 (week 0)	Test visit 2 (week 6)	Test visit 3 (week 12)
Screening questionnaire	X			
Demographic data	X			
Medication, health status and any changes	X	X	X	X
Informed consent	X			
Height and weight	X	X	X	X
Waist circumference and hip circumference	X	X	X	X
Body composition (bioelectric impedance)	X	X	X	X
Blood pressure	X	X	X	X
Blood sample	X	X	X	X
Allocation		X		
Physical activity questionnaire		X	X	X
Mini-mental State Examination		X		X
24-h diet recall		X	X	X
Spot urine sample	X	X		X
Faecal sample		X		X
Provided supply of capsules		X	X	
Tablet count			X	X
Compliance assessment			X	X
Assess adverse reactions			X	X
Collect unused test product			X	X

**Table 2 Tab2:** Biological and anthropometric parameters analysed in the lutein supplementation study

	Variable	Screening (−4 week)	Test visit 1 (week 0)	Intermediate visit (week 6)	Test visit 2 (week 12)
Biological	TC	X	X	X	X
	TGs	X	X	X	X
	HDL-C	X	X	X	X
	LDL-C	X	X	X	X
	ALT	X	X	X	X
	AST	X	X	X	X
	Creatinine	X	X	X	X
	FBG	X	X	X	X
	Insulin	X	X	X	X
	Lutein	X	X	X	X
	RBP4		X		X
	Adiponectin		X		X
	IL-6		X		X
	IL-1β		X		X
	CRP		X		X
	MCP-1		X		X
	TNF-α		X		X
Anthropometric measurement	WC	X	X	X	X
	HC	X	X	X	X
	BMI	X	X	X	X
	WHR	X	X	X	X
	WHtR	X	X	X	X
	BP	X	X	X	X

*Abbreviations*: *ALT* alanine aminotransferase, *AST* aspartate aminotransferase, *BMI* body mass index, *BP* blood pressure, *CRP* C-reactive protein, *FBG* fasting blood glucose, *HC* hip circumference, *HDL-C* high-density lipoprotein cholesterol, *IL* interleukin, *LDL-C* low-density lipoprotein cholesterol, *MCP-1* monocyte chemoattractant protein-1, *RBP4* retinol-binding protein 4, *TC* total cholesterol, *TG* triglyceride, *TNF-α* tumour necrosis factor-alpha, *WC* waist circumference, *WHR* waist-to-hip ratio, *WHtR* waist-to-height ratio

#### Test visit

At test visit 1 (week 0), eligible participants will be allocated to either a lutein supplement group or a control group. The lutein supplement group will take one 10 mg lutein capsule daily, and the control group will take the placebo. Participants will be given a 6-week supply of capsules at both visit 1 and visit 2 and will be required to return the remaining capsules at the next visit, which will be counted and recorded for each participant to ensure compliance with the protocol. Participants will be defined as non-compliant if they took less than 80% of the study product. Medication, health status or any recent changes around the inclusion and exclusion criteria since the completion of the screening questionnaires will also be re-assessed to evaluate whether participants are still suitable to participate in the study. Anthropometric measurements, dietary assessments and blood samples will be collected at each visit, and stool samples and spot urine samples will be collected at test visit 1 and test visit 3. At test visit 1 and test visit 3, the volunteers will be asked to complete the short form of the International Physical Activity Questionnaire (IPAQ-short form) and the Mini-mental State Examination (MMSE). At the end of each visit, participants will be thanked for their time and will be provided with breakfast. After test visit 3, people in the placebo group will be given the same amount of lutein supplements as that provided to the intervention group. The full details of the data that will be collected at each time point can be found in Table 1.

